### ***Concomitant Medications:***

Although there will be no restrictions of ancillary treatments, the names, doses preparations, indications and duration of use of such medications will be properly documented. Concomitant treatment with antiretroviral will be a reason for exclusion/withdrawal from the study.

## 3.5 Treatment Allocation

Patients are to be allocated to the different treatment arms according to a computer generated randomisation list. The randomisation list will be prepared and kept by the Study Director. Each centre will be provided with a batch of sealed envelopes. The total number of allocated envelopes will correspond to their expected intake to the study. Therefore, each patient will be allocated randomly **either** the FDCs regimen **or** the separate drug regimen. Each sealed envelope will contain a sequential patient code (randomisation number) and a Treatment Card printed with the details of one of the two regimens to which the patient will be allocated. Only a specially assigned person will open the envelope and dispense the drugs to the patient. No other study personnel will be present at the time of drug allocation. This information will, therefore, only be known to the assigned dispenser and the patient. Randomisation is considered to have taken place once the envelope containing the code for the drug regimen is opened. Once a patient is allocated a randomisation number must not be used for other patients, in the event that the patient decides to withdraw voluntary consent before study drug administration. A treatment allocation log will be kept by the specially assigned person and will not be available to the investigators until the analysis has been concluded, or unless the patient’s physician requires this information for safety reasons.

The PI and the clinicians will remain blinded to the drug regimens of individual patients throughout the study.

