# 4. STATISTICAL CONSIDERATIONS

The objective of the study is to demonstrate that FDCs have equivalent efficacy to the loose formulations.

Sample sizes of 498 from the intervention group and 498 from the standard group achieve 90%

power at a 5% significance level using a one-sided equivalence test of proportions when the

proportion of patients cured in the comparator group (Ps) is 96% and the maximum allowable difference (clinically acceptable difference) between proportions in the two treatment groups that still results in equivalence (the range of equivalence) is 4%. A sample size of 498 in each group is estimated with dropout rates of 10%. Two study sites will conduct the trial and contribute to the total sample size. Ethiopia will contribute a total of 498 subjects (249 in each arm) per country to reach the sample size of 996.

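### The randomisation number is sealed inside an envelope opened by an unblinded dispenser with no other staff present, so no patient is tied to an envelope before its regimen is known

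*Protocol*

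**What the plan says.** Protocol section 3.5 (Treatment Allocation) sets out the envelope procedure in some detail.

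- List: it is computer generated, and "The randomisation list will be prepared and kept by the Study Director". Each centre receives a batch of sealed envelopes sized to its expected intake.
- Content: "Each sealed envelope will contain a sequential patient code (randomisation number) and a Treatment Card" showing one of the two regimens. No number on the outside is mentioned.
- Opening: "Only a specially assigned person will open the envelope and dispense the drugs to the patient", and "No other study personnel will be present at the time of drug allocation".
- Moment of allocation: "Randomisation is considered to have taken place once the envelope containing the code for the drug regimen is opened".
- Record: the dispenser keeps the allocation log. Investigators may see it only after the analysis is finished, except where a physician needs the information for safety. A number already given to a patient may not be reused.

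Section 3.5 states no rule that envelopes are opened in order. It also asks for no record of patient, date or time before opening.

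Other sections bear on this. Section 3.3 blinds investigators, laboratory staff and analysts, and separates dispensing from clinical management. Section 6.1 makes the randomisation number and the sample date identifiers on forms and specimens. Section 6.2 provides for sponsor monitoring visits with source data verification.

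**The concern.** Sealed envelopes conceal allocation only if the patient is committed to a particular envelope before anyone knows what is in it. Here the only sequence number is hidden until the seal is broken, and breaking the seal also shows the regimen. The person who does this works without a colleague present, knows which regimen is which, and writes the log. Section 3.5 does not stop that person from opening a later envelope first, or from opening two and giving the patient the one preferred. The ban on reusing a number does not help, because it applies only once a number has been given to a patient.

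The regimens differ visibly in tablet burden. Sections 2.1 and 1 of the Protocol themselves present tablet burden as a threat to compliance, and treatment completion is a secondary outcome. A well-meaning dispenser could think that a frail or reluctant patient would do better on fewer tablets. What is at stake is selection bias in the cure comparison, which is judged against a margin of only 4 points and which adjustment for recorded covariates cannot be relied on to repair.

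**Working it through.** **1. The plan's own sample size.** Section 4 gives 498 per arm for 90% power, one-sided 5%, 96% cure, a 4-point margin and 10% dropout. With the restricted-likelihood (Farrington-Manning) null variance, the null proportions are 0.932 and 0.972:

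n = [(1.645 × √(0.932×0.068 + 0.972×0.028) + 1.282 × √(2×0.96×0.04)) / 0.04]² ≈ 452 per arm.

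Dropout takes this to 452/0.9 ≈ 502 or 452×1.1 ≈ 497. The stated 498 is reproduced closely, so the planning inputs can be used below.

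**2. Tablets a day in the intensive phase (section 3.4).**

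| Weight | FDC | Loose drugs |
|---|---|---|
| 40-54 kg | 3 | 2+1+1+3 = 7 |
| 55-70 kg | 4 | 3+1+1+3+4 = 12 |

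**3. Size of a possible bias. All steering inputs are assumptions; the Protocol gives none.** Let f be the fraction of all patients subject to steering, d their shortfall in cure rate, and s the completeness of steering (0 = chance, 1 = all in one arm). Arms stay at 498, because patients are exchanged between envelopes. Of the 996f such patients, 498f would fall in each arm by chance. Steering makes this 498f(1+s) and 498f(1−s), so

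bias = 2 × f × s × d.

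With f = 5% (about 50 patients) and d = 20 points:
- s = 0.5: about 37.5 v 12.5 patients; 25/498 × 20 = 1.0 point.
- s = 1: 50 v 0 patients; 50/498 × 20 = 2.0 points.

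Range over other assumptions, half-complete to complete steering, in points:

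| f | d = 10 | d = 20 | d = 30 |
|---|---|---|---|
| 2% | 0.2 to 0.4 | 0.4 to 0.8 | 0.6 to 1.2 |
| 5% | 0.5 to 1.0 | 1.0 to 2.0 | 1.5 to 3.0 |
| 10% | 1.0 to 2.0 | 2.0 to 4.0 | 3.0 to 6.0 |

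**4. Effect on the conclusion.** Take 448 per arm (498 × 0.9), one-sided 5% and unpooled variance.

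*Weaker patients steered to FDC, no true difference.* SE = √(2×0.96×0.04/448) = 0.0131. Power = Φ((0.04 − bias)/SE − 1.645).
- No bias: 92%.
- 1 point: 74%.
- 2 points: 45%.

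*Weaker patients steered to loose drugs, FDC truly 4 points worse (92% v 96%).* SE = √((0.96×0.04 + 0.92×0.08)/448) = 0.0158. Chance of a false claim = 1 − Φ(1.645 − bias/SE).
- No bias: 5%.
- 1 point: 16%.
- 2 points: 35%.

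**The case against.** Several safeguards exist. In the recruitment flow chart, eligibility and consent precede allocation. Section 3.3 blinds the investigators, so the dispenser does not decide who enters and those who recruit do not learn the allocation. That closes the commonest route to selection bias. It does not close this one, because the dispenser can still choose which envelope an enrolled patient receives.

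All doses are directly observed, which weakens the link from tablet burden to cure. The one motive the documents suggest, sparing weaker patients a heavy tablet load, would work against FDC. It would cost power rather than produce a false claim of equivalence. Both points stand and limit the seriousness. The documents give no evidence that anyone would steer patients.

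A reader might infer that manipulation would leave no trace. The documents do not support that. The Study Director holds the list, numbers are sequential and not reused, forms and specimens carry number and date, and monitors verify source data. Section 3.5 withholds the log from investigators but does not say that it is withheld from the monitor. Taking a later envelope first would often put numbers out of step with enrolment dates. The check is still incomplete: time of opening is not recorded, so exchanges among patients enrolled close together, or an envelope opened early and held back for its turn, would escape. It also acts only after the event.

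A reader might also infer that the planned 249 per arm per country in section 4 is endangered. That does not follow. A batch of 249 + 249 envelopes used in full gives 249:249 in any opening order. The Protocol does not say that the list is unblocked, and such detail may sit in a randomisation plan. Even under simple randomisation, a split of 529:467 (the edge of the 95% range for 996 patients) gives 92.00% power after dropout against 92.09% for equal arms.

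**Conclusion.** The procedure in section 3.5 has a real concealment weakness. The number and regimen are revealed together, to one unblinded person with no other staff present, who also keeps the log. Selective allocation is not prevented, and only part of it could be found later. This is a matter of what the Protocol fixes, rather than detail left to another document.

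The size is not known. The figure of 1 to 2 points rests wholly on assumed inputs (5% steered, cure 20 points lower) and would be a quarter to a half of the 4-point margin. Under the motive that the documents make plausible, the main harm is lost power. A raised risk of a false claim of equivalence needs steering in the opposite direction. The change should be made because it is cheap and because the problem cannot be dependably repaired at analysis.

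**What to change.** Amend section 3.5 as follows.

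1. Use opaque sealed envelopes with the sequence number printed on the outside.
2. After consent and confirmed eligibility, blinded enrolling staff take the lowest-numbered unopened envelope. They write the patient identifier, date and time on it and on the screening log, then hand it to the dispenser.
3. The dispenser opens envelopes strictly in order and only when they are so marked. A marked envelope is never passed to another patient.
4. Keep all envelopes, opened and unopened.
5. At the visits already planned in section 6.2, the sponsor's monitor reconciles them with the screening log and the Study Director's list.

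Blinding is kept, since the outside shows only a number that section 6.1 already places on every form and specimen. The cost is a printing change, one log line per patient, a check at existing visits and slightly more handling at enrolment. No extra staff are needed.

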**3.6 Study conduct**

The flow of patients is illustrated in the flow chart (Annex ). Patients will be seen by the clinic physicians as per the clinic routine. From this consultation, any smear positive cases of pulmonary TB will be referred to the research team to assess eligibility. Consenting patients will undergo full assessment as detailed in the CRF. This will include: (i) sputum culture, (ii) HIV counselling and testing (including CD4 count), (iii) a full blood count, (iv) liver function tests (SGOT, SGPT, alkaline phosphatase, direct and total bilirubin, albumin), fasting blood sugar (v) renal function tests (creatinine, blood urea nitrogen), and (vi) a urinary pregnancy test, uric acid and urinary glucose, protein, bilirubin and urobilinogen.

Sputum specimens for direct smear will be collected on Day 0, Weeks 8, 20, and 24 (See table). At each of these times three sputum specimens will be provided: after deep cough: one spot, one morning and a second spot specimen. A patient is considered smear negative if: (i) all 3 consecutive sputum smears are read as negative, or (ii) 4 out of 5 are read as negative in the event that only two of the first three smears was negative. (Note: with TB co-infected HIV patients, more patients are smear negative).

Culture will be done on Day 0 and weeks 8 and 24. A culture and sensitivity at week 20 will only be done if sputum samples of the same week are positive. Sensitivity test on the stored sputum samples from week 0 will also be done if sputum samples at week 20 are positive. A minimum of three sputum samples will be required from each patient at each of these time points. Sample collection will be done on days when patients come to collect their drugs. Cultures will be inoculated from pooled sputum samples.

For the purpose of defining the cure and relapse rates, only the sputum culture result will be used. Standard operating procedures have been prepared for collection, storage, transport, and testing of culture samples before the study starts.

Time frame for the duration of the study:

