### ***Primary Outcome measures***

- cure rates at end of treatment (6 months). A cure is defined as one negative sputum culture in patients who did not fail treatment. A treatment failure is defined as:

1. a patient who is persistently smear positive by five months of treatment
2. a patient who becomes smear negative but positive again at or after five months of treatment (note: sputum positivity before this time is not considered a treatment failure)

- ***Secondary outcome measures***
- early response rates: proportion of patients with negative culture results at 8 weeks after initiation of therapy
- proportion of patients with relapses during the 72 weeks follow up period after the end of treatment. A relapse is a patient previously treated for tuberculosis who has met the case definition of cure (as defined above) and been declared cured by a physician and who has now been diagnosed with bacteriologically positive (two positive smears and culture positive) tuberculosis. If there is discordance between smear and culture results, a clinical decision will be made regarding further management: (i) smear positive, culture negative, and (ii) smear negative and culture positive.
- cure rates in HIV positive TB patients
- proportion of patients with clinical deterioration of pulmonary tuberculosis with the need for hospitalisation
- proportion of patients with *serious* adverse events any time during chemotherapy
- proportion of patients with any adverse events during chemotherapy
- proportion of patients completing treatment (defined as patients who achieved a total of 54 out of 56 doses in the first eight weeks of treatment AND 107 out of 112 doses at a daily rate during the subsequent 16 weeks of treatment) within each group. (96% doses taken considered as completed in intensive and maintenance phases).
- Proportion of patients who developed MDR-TB

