**Week 36 Week 48 Week72 Week 96**

(End of trial)

| Study procedures | Screening | Enrolment  Study Drug  T=0h | Week 8  (end of intensive phase) | Week  20 | Week 24  (end of continuation phase) | (Weeks 36,48,72 and 96) |
| --- | --- | --- | --- | --- | --- | --- |
| Medical History | X |  |  |  |  |  |
| Physical Examination | X |  | X | X | X | X |
| Sputum for AFB smear | X |  | X | X | X | X |
| Sputum for culture |  | X | X | Xa | X | Xa |
| Sensitivity testing |  |  |  | Xb |  |  |
| Informed consent | X |  |  |  |  |  |
| Haematology and Clinical chemistry | X | X | X | X | X | X |
| Urine analysis | X | X |  |  |  |  |
| Pregnancy test | X |  |  |  |  |  |
| HIV testing  CD4 test | X  Xd |  |  |  | Xd | Xd |
| Randomisation |  | X |  |  |  |  |
| Drug administration |  | X | X | X | Xe |  |
| Adverse Events |  | Symptom checklist | X | X | X | X |

Xa It the sputum smear is positive

Xb Sensitivity testing of screening smear and 5 month smear if sputum is positive.

Xd CD4 testing only for HIV positive TB patients. Repeat CD4 test on weeks 24, 48, 72 and 96. Not indicated at week 36.

Xe By the end of week 24, treatment should be completed.

Patients will be instructed to attend the TB treatment centre, for the duration of treatment; both the intensive and maintenance phases. All drug doses will be administered under observation and documented by the trial nurse. All drug doses in the continuation phase will be administered under standard operation of DOTS of the country. Patients will also be evaluated for clinical, haematological and biochemical parameters during these follow up period.

Trial subjects will be followed up for 72 weeks after the completion of treatment. They will be required to come to TB treatment centre for clinical, haematological and biochemical assessments at the end of 36 weeks ,48 weeks ,72 weeks and 96 weeks after initiation of treatment. A home visitor will trace individuals who fail to come at the specified time points. At each follow-up time, subjects will provide three sputum samples: one spot, one morning and a second spot sputum specimens for smear examination at each of the three follow up visits. Cultures will be done only for smear positive individuals (as defined above).

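### Cure, the primary endpoint, has two conflicting definitions: smear-defined failure rules it out in section 2.2, but only culture counts in sections 3.6 and 6.4

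*Protocol*

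**What the plan says.** **Cure.** Protocol section 2.2 (Primary Outcome measures) sets the endpoint at the end of treatment, six months: "A cure is defined as one negative sputum culture in patients who did not fail treatment". It gives two criteria for failure, both based on smear alone: "a patient who is persistently smear positive by five months of treatment", and "a patient who becomes smear negative but positive again at or after five months of treatment".

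Section 3.6 (Study conduct) gives another rule: "For the purpose of defining the cure and relapse rates, only the sputum culture result will be used". Section 6.4 (Data analysis) follows section 3.6. Its primary comparison is a chi-square test of culture-positive against culture-negative patients, placed at study end. The time line in section 3.6 puts the end of the trial at week 96.

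**Relapse.** Section 2.2 requires a previously cured patient to have "bacteriologically positive (two positive smears and culture positive) tuberculosis". Section 3.6 again says culture only.

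**Specimens.** "Culture will be done on Day 0 and weeks 8 and 24"; at week 20 culture is added only after a positive smear. At the follow-up visits (weeks 36, 48, 72 and 96): "Cultures will be done only for smear positive individuals (as defined above").

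**The concern.** These are two rules for the same endpoint, and the word "only" in section 3.6 leaves no room for the smear-based exclusion in section 2.2. Some patients would be counted as failures by one section and as cures by another. The cure count, the cure rate in each arm and the denominator for relapse all depend on which section is followed.

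The timing in section 6.4 adds a second inconsistency. Taken literally, study end is week 96, when culture is done only in smear-positive patients. A comparison of culture results at that visit would not be the six-month cure rate named in section 2.2.

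Cure is expected to be high and non-cures few, so a small number of reclassified patients is a visible share of the events.

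**Working it through.** **1. Classification at end of treatment.** Smear is read at weeks 20 and 24, and culture is taken in everyone at week 24. The two failure criteria together cover every patient with a positive smear at week 20 or 24: either the smear has stayed positive, or it became negative and turned positive again.

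| Smear at week 20 or 24 | Culture at week 24 | Section 2.2 | Sections 3.6 and 6.4 (read at week 24) |
|---|---|---|---|
| negative | negative | cured | cured |
| negative | positive | not cured | not cured |
| positive | positive | not cured | not cured |
| positive | negative | **not cured (failure)** | **cured** |

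Only the last row conflicts, and always in the same direction. Such patients remain in the trial: the withdrawal list in section 3.2 and the MDR flow chart remove a week-20 smear-positive patient only when resistance to isoniazid and rifampicin is confirmed. The others go on to the week-24 culture.

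**2. The plan's own figure.** Section 4 gives 498 per arm for 90% power, one-sided 5%, 96% cure, a 4-point margin and 10% dropout. With the Farrington-Manning (restricted maximum likelihood) variance:

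- restricted estimates under the null: 0.972 and 0.932
- v0 = 0.972 × 0.028 + 0.932 × 0.068 = 0.0906
- v1 = 2 × 0.96 × 0.04 = 0.0768
- n = (1.645 × √0.0906 + 1.282 × √0.0768)² / 0.04² ≈ 452
- 452 × 1.10 = 497.2, so 498. The stated figure is reproduced.

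**3. Size of the conflict.** Evaluable per arm: 498 × 0.90 ≈ 448. Expected non-cures: 448 × 0.04 = 17.9, about 18. Each 1% of smear-positive, culture-negative patients is 448 × 0.01 = 4.5 per arm. The protocol gives no such rate, so 1% and 2% below are assumptions.

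Suppose the 96% is the culture-only rate and discordance is equal in both arms. The half-width is 1.645 × √(2p(1−p)/448).

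| Discordant (assumed) | Patients moved per arm | Cure rate under section 2.2 | One-sided 95% half-width | Power at 448 per arm |
|---|---|---|---|---|
| 0% | 0 | 96% | 2.2 points | 90% |
| 1% | 4.5 | 95% | 2.4 points | 84% |
| 2% | 9.0 | 94% | 2.6 points | 79% |

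The expected difference between arms stays at zero in every row. If the 96% is instead the section 2.2 rate, culture-only cure would be higher than 96% and power would rise. Section 4 does not say which rule the 96% refers to.

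**4. Relapse.** Follow-up culture is taken only after a positive smear, and smear-positive already means at least two positive specimens (section 3.2). The two relapse rules therefore give nearly the same observed numerator. A smear-negative, culture-positive recurrence would count under section 3.6 and not under section 2.2, but no culture is taken to detect it. The denominator, patients previously cured, carries over the conflict in step 1.

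**The case against.** The strongest defence is to read the sections in sequence: remove smear-defined failures first, then use culture to confirm cure in the rest. That would reconcile cure, but section 3.6 says culture alone defines it, and section 6.4 analyses culture alone with no exclusion for smear failure.

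A second defence is that section 6.5 requires the analytical plan to be final before the analysis phase, and section 3.3 blinds those who analyse the data. This stands in part. It weakens any suggestion that the definition could be picked to favour an arm, and a separate plan may already have settled it. It does not remove the contradiction, because the protocol states both rules.

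Three stronger readings are tempting, and the document does not support them:

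- *A patient culture-negative at week 8 and culture-positive at week 24 would count as cured, because no time point is attached to the negative culture.* Section 2.2 places cure at the end of treatment, section 3.6 schedules a week-24 culture for all, and the week-8 culture is a separate secondary outcome. Such a patient is not cured under either rule; he or she merely lacks a named failure category.
- *The reclassified patients can be set directly against the 4-point margin.* The margin concerns the difference between arms. Equal reclassification in both arms leaves that difference unchanged in expectation.
- *The discordance clause shows that smear-negative relapse was meant to be counted.* The clause reads "If there is discordance between smear and culture results, a clinical decision will be made regarding further management". It governs management and assigns no endpoint category.

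The share of events affected also depends on the analysis set. Section 3.2 keeps withdrawals and losses in the intention-to-treat set. If the 10% dropouts counted as not cured (an assumption), non-cures would be about 50 + 18 = 68 per arm, and 4.5 to 9 reclassified patients would be 7% to 13% of them.

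**Conclusion.** The primary endpoint is contradictory as written. Patients with a positive smear at week 20 or 24 and a negative culture at week 24, and not withdrawn as MDR, are not cured under section 2.2 and cured under sections 3.6 and 6.4. Section 6.4 also points to a visit other than the six-month one.

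The size cannot be fixed from the protocol. Each assumed 1% of such patients moves 4 to 5 per arm, where about 18 non-cures are expected among 448 evaluable. At equal rates this alters the reported cure rate and the precision; nothing in the protocol shows that it biases the comparison.

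For relapse the conflict is mainly one of text. What remains is that smear-negative relapse is not ascertained. This deserves a plain statement because section 3.6 itself notes that more patients with HIV co-infection are smear-negative.

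**What to change.** - **Cure.** State one rule, tied to the week-24 culture, that says explicitly whether smear-defined failure at or after month five overrides a negative culture. Use it in sections 2.2, 3.6 and 6.4. Changing section 3.6 alone would leave the contradiction in section 6.4.
- **Timing.** In section 6.4, replace the reference to study end with week 24.
- **Sensitivity analysis.** Report cure under the other definition as well, so that readers can see how many patients change class in each arm.
- **Sample size.** State in section 4 which definition the 96% refers to.
- **Relapse.** Bring section 3.6 into line with section 2.2, label the outcome smear-positive, culture-confirmed relapse, and state that smear-negative, culture-positive relapse is not ascertained under the follow-up schedule.

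The cost is an amendment to wording and one extra analysis. No new specimens or visits are needed. The relapse claim becomes narrower, to match what is measured.
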